## Discussion

The presentation of the study protocol covering design, outcome measures, sample size calculations, and procedures of this RCT on early skin-to-skin for very preterm infants, is in accordance with the Standard Protocol Items: Recommendations For Interventional Trials (SPIRIT) 2013 statement for clinical trial protocols Additional file 1 [40].

Bayley Scales of Infant and Toddler Development, Third Edition (Bayley-III) at 2 years of corrected age is chosen as the primary outcome measure. Although many interventions in the neonatal period appear to have short-term beneficial effects [15, 23, 41, 42], such effects seem to disappear over time [15, 43]. The complexity of neurodevelopment and the genetic, epigenetic, and environmental factors, which may influence the development, makes it less likely that a single, short-lasting intervention will lead to a change in cognition and/or behavior after 2 years. Thus, any intervention offered to these infants must be followed over time to learn more about their potential effects or lack of such.

In order to assess developmental delay in the children at the corrected age of 3 months and 2 years, the ASQ-SE is used [38]. This screening instrument is found to be valid in identifying of social and emotional difficulties in children [44]. Preterm delivery is associated with maternal anxiety and stress [45–47], and the effect of separation of the mother and her very preterm infant is not well studied. We have chosen to assess this aspect by using the STAI, which is validated in a Norwegian population and found reliable in terms of assessing anxiety in women [34].

Lately, there has been a shift toward a more gentle initial handling of preterm neonates. This view is well described by Jobe and colleagues, who argue that the majority of preterm infants need only supportive treatment in the transition to the extrauterine life, and not resuscitation [48, 49]. The main focus of this approach has, so far, been on early CPAP [50, 51], less invasive ways of surfactant administration [52, 53], avoidance of early mechanical ventilation [54], and maintenance of adequate body temperature [55]. In line with this, facilitation of early skin-to-skin contact between the preterm infant and the mother could contribute to a more gentle adjustment to extrauterine life with improved physiological stability. The results from this study will have important implications for how we care for very preterm infants immediately after delivery. It will also increase our understanding of how early SSC affects very preterm infants and their mothers.

Those who are conducting the Bayley-III and the GMA will be masked to the intervention group, but not the parents and NICU staff caring for the baby in the first 24 hours. Parents in the SSG group may continue to have an increased focus on SSC, and this could potentially extend the total skin-to-skin time in the NICU. However, this limitation seems inevitable with the intervention in question.

### Trial status

The study is currently recruiting participants. Since study start February 1, 2014 and through June 2016, 67 eligible pregnant women have been admitted to the maternity ward at St. Olav’s Hospital. A majority of these did not deliver before 32 weeks of gestation. Up to June, 2016, 27 infants have been included in the study.

From January 1, 2017, two other hospitals in Norway will participate in the study: Drammen Hospital, located in the eastern part of Norway, and Kristiansand Hospital in the southern part. Between 30 and 35 infants with GA <32 weeks are born every year at each of these hospitals. Based on this, the estimated time for end of inclusion will be 2018.

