## Methods/Design

### Project context

The study is currently being carried out at St. Olav’s University Hospital in Trondheim. Trondheim is the third largest city in Norway, and St. Olav’s Hospital serves a population of almost 446,000 and is a tertiary care center for preterm infants <30 weeks of gestation. Approximately 50 infants with GA <32 weeks are born every year at St. Olav’s Hospital.

The NICU at St. Olav’s Hospital has 21 beds, with seven beds for intensive care, seven intermediate, and seven in a step-down unit. Altogether, there are 107 nurses (many part-time) and six consultants working in the NICU. The maternity ward has two sections with seven delivery rooms each and about 120 midwives employed.

Delivery rooms are in the same building as the NICU, but on separate floors (fifth and second floor, respectively). The operating room and the postoperative ward are in the same building and at the same floor as the NICU.

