#### Randomization and allocation concealment

The randomization is done after the initial stabilization of the infant (Fig. 1). Infants are stratified by weeks of gestation (28^0^–29^6^ and 30^0^–31^6^). The randomization is conducted using sealed envelopes organized by the Unit for Applied Clinical Research at the NTNU.

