#### Sample size and statistical analyses

Primary analysis: sample size calculations are performed for a two-sample *t* test for comparing the Bayley Scale of Infant and Toddler Development, Third Edition, cognitive scale between the intervention (SSC) and control (SC) groups at 2 years of corrected age. To obtain a power of 80% for detecting a difference of 7.5 in mean score, using SD = 15 and significance level α = 0.05, 64 preterm infants are needed in each group. To allow for withdrawals, the sample size is set to 68 in each group.

Secondary analysis: differences between the SSC and SC groups for continuous variables will be analyzed using two-sample *t* tests, or Mann-Whitney *U* tests for data with non-normal distributions. Categorical variables will be analyzed by the Pearson chi-square test or Fisher’s exact test. *P* values <0.05 are considered statistically significant. Due consideration of multiple testing will be made when interpreting the results. All data will be presented and analyzed in accordance with the updated CONSORT guidelines for randomized trials [39].

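### Two hospitals join in January 2017, but the stated randomisation strata and tests leave centre out: no bias on average, but avoidable chance imbalance and a small loss of power

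*Protocol article*

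**What the plan says.** Project context sets the trial at a single hospital: "The study is currently being carried out at St. Olav’s University Hospital in Trondheim".

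Randomization and allocation concealment names one stratification factor, "Infants are stratified by weeks of gestation", in two bands (28^0^–29^6^ and 30^0^–31^6^). On the mechanism it says "The randomization is conducted using sealed envelopes organized by the Unit for Applied Clinical Research at the NTNU". It mentions neither centre nor separate envelope sets by hospital.

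Sample size and statistical analyses gives the primary comparison through its sample size: "sample size calculations are performed for a two-sample *t* test for comparing the Bayley Scale of Infant and Toddler Development, Third Edition, cognitive scale". Secondary continuous outcomes "will be analyzed using two-sample *t* tests, or Mann-Whitney *U* tests for data with non-normal distributions", and "Categorical variables will be analyzed by the Pearson chi-square test or Fisher’s exact test". No covariate or stratified test is named.

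Trial status then makes the trial a three-centre one: "From January 1, 2017, two other hospitals in Norway will participate in the study". It gives 30 to 35 births below 32 weeks a year at each new hospital (Project context gives about 50 at the first) and expects inclusion to end in 2018.

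**The concern.** The stated randomisation and tests suit a one-hospital trial, and the announced trial has three hospitals. The first hospital is a tertiary centre for infants below 30 weeks, which is also the boundary between the GA strata. The simulation training described took place there before the 2014 start. Delivery-room staff are unmasked. Centre could therefore plausibly be related to case mix, delivery of the intervention, early temperature and physiology, and developmental scores.

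Two things are at stake. If nothing balances centre, the arms can by chance hold different shares of new-site infants, and the single estimate the trial produces moves with any centre difference. Whether or not allocation is balanced, a test that ignores centre leaves centre variation in its error term.

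**Working it through.** **1. The plan's own figure.** Difference 7.5, SD 15, α = 0.05 (taken as two-sided; the article does not say), power 80%. The exact two-sample t calculation gives 63.8 per group, rounded up to 64, with power 80.1%. The stated 64 is reproduced. The allowance to 68 corresponds to 1 − 64/68 = 5.9% withdrawals.

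**2. Share of infants from the new hospitals.** Inputs: 27 infants in 29 months (February 2014 to June 2016) and the annual births quoted above. Assumption: the new hospitals recruit at the first hospital's yield.
- Yield: 27 / (50 × 29/12) = 22.3% of births.
- First hospital: 27/29 × 12 = 11.2 a year, so 27 + 5.6 = 32.6 infants by the end of 2016.
- Both new hospitals together: 2 × 30 × 0.223 = 13.4 to 2 × 35 × 0.223 = 15.6 a year.
- By the end of 2018: 32.6 + 2 × (11.2 + 13.4 to 15.6) = 82 to 86 infants, of whom 27 to 31 (33-36%) come from the new hospitals, or 13 to 16 each.
- If recruitment instead runs to 136: (136 − 32.6)/24.6 = 4.2 years or 103.4/26.8 = 3.9 years from January 2017. The new hospitals then supply 56 to 60 infants (41-44%), or 28 to 30 each.

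**3. Chance imbalance if nothing balances centre.** With 68 of 136 infants in each arm and m from the new hospitals, the number x of those in the skin-to-skin arm is hypergeometric. Its variance is (m/4)(136 − m)/135, and the difference in new-site share is (2x − m)/68.

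| New-site share | m | Chance of ≥10 points | Chance of ≥15 points | 95th percentile |
|---|---|---|---|---|
| 30% | 41 | 26% | 6% | 16 points |
| 40% | 54 | 22% | 5% | 18 points |
| 50% | 68 | 23% | 6% | 18 points |

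At a single hospital with 29 infants the SD of x is √(29/4 × 107/135) = 2.4, and the 95% range is 10 to 19.

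**4. Effect on the estimate.** Shift = imbalance × centre difference. The article gives no centre difference, so 3, 5 and 7.5 Bayley points are assumed. At the 95th percentile:
- 3 points: 0.16 × 3 to 0.18 × 3 = about 0.5
- 5 points: 0.8 to 0.9
- 7.5 points: 1.2 to 1.3

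**5. Type I error and power.** 128 infants, half from the new hospitals, within-centre SD 15, 20,000 simulated trials per setting, centre difference 5 or 7.5 points.

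| Allocation | Analysis | Type I error | Power |
|---|---|---|---|
| Not balanced by centre | t test | 4.7-5.4% | 78-79% |
| Not balanced by centre | Linear model with centre | 4.8-5.3% | 80% |
| Balanced by centre | t test | 4.3-4.7% | 79% |
| Balanced by centre | Linear model with centre | 5.0% | 80-81% |

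The third row can be checked by hand. With balance the true variance is 225, but the t test estimates 225 + 7.5²/4 = 239.1 (or 225 + 5²/4 = 231.3). The effective critical value rises from 1.979 by a factor √(239.1/225) = 1.031 to 2.040, which gives 4.3%. For 5 points the factor is 1.014, which gives 4.7%.

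If the planning SD of 15 already includes variation between centres, the t test keeps 80.1%. What is lost is then a forgone gain: within-centre SD √(225 − 6.25) = 14.79 gives 81.2%, and √(225 − 14.06) = 14.52 gives 82.6%. Either way the difference is about 1 to 2.5 points.

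**The case against.** The strongest reply is that the point rests on silence. The new hospitals appear in a forward-looking status note, and a journal article commonly leaves envelope logistics, block structure and covariates to the full protocol or analysis plan. A clinical research unit runs the envelopes. They are opened just after stabilisation, so each hospital must in practice hold its own set; if those sets are blocked, arms will be roughly balanced within hospital. GA, one route by which centres might differ, is already a stratum. The training section concerns the 2014 start and says nothing about training at sites that join later.

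Much of this stands. A reader might infer that randomisation definitely continues unchanged after January 2017, or that nothing will balance the arms within a hospital. The article says neither, so the imbalance figures describe what happens if the stated scheme is carried over without centre balance. A reader might also infer that centre confounds the comparison. It does not: chance imbalance averages to zero over randomisations, and type I error stays near 5%. Nor should 28 to 30 infants per new hospital be taken as the expected contribution: at the observed yield, stopping at the end of 2018 gives 13 to 16 each.

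What does not fall away is that the article does more than omit detail. It names its stratification factor and its tests, then announces a change of design that neither reflects. Site-specific blocked envelopes would not settle the matter alone, because the stated t test would then be slightly conservative.

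**Conclusion.** The point holds at modest size. Centre is absent from both the stated strata and the stated tests of a trial that becomes multicentre. The estimate remains unbiased on average and type I error is not inflated; the documents do not support a stronger claim.

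The exposure is a conditional one in the one trial that will be run: a 22-26% chance of a new-site imbalance of at least 10 percentage points, and a shift of up to about 0.5 to 1.3 Bayley points at the 95th percentile. Added to that is a power cost of about 1-2 points. The imbalance figures assume a total of 136 and a new-site share of 30-50%; in a smaller trial the percentage-point imbalance would be more variable. The shifts and power losses depend on assumed centre differences of 3 to 7.5 points, for which the article gives no figure. The case for acting is that the remedy is cheap and that balanced allocation cannot be restored once new-site infants have been randomised.

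**What to change.** Before the new hospitals start:

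- **Randomisation.** State that each hospital receives its own sealed-envelope sets within each GA stratum, in small blocks of varying size that are concealed from site staff.
- **Primary analysis.** Compare the Bayley-III cognitive score between arms in a linear model with centre and GA stratum as fixed effects, in place of the plain t test. Use the same model for continuous secondary outcomes where a linear model is suitable.
- **Other outcomes.** One added model term does not fit Mann-Whitney, chi-square or Fisher tests. Keep the stated tests for sparse binary safety outcomes, with a centre-stratified analysis as a sensitivity check where event counts allow.

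The cost is printing the envelope sets and revising the analysis text; the required sample size does not change. The downside is six small strata instead of two (at 13 to 16 infants per new hospital by the end of 2018, about 7 in each GA stratum if evenly split). Small blocks also make allocation somewhat more predictable in an unmasked trial. Varying and concealing the block size eases this but does not remove it.

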## Abbreviations

AMR: Assessment of Motor Repertoire
ASQ-SE: Ages & Stages Questionnaire - Social-Emotional
Bayley-III: Bayley Scales of Infant and Toddler Development, Third Edition
BPD: Bronchopulmonary dysplasia
CPAP: Continuous positive airway pressure
CRF: Case report form
CRP: C-reactive protein
DR: Delivery room
FFC: Family-centered care
GA: Gestational age
GMA: General Movement Assessment
IVH: Intraventricular hemorrhage
KC: Kangaroo care
NEC: Necrotizing enterocolitis
NICU: Neonatal intensive care unit
NIDCAP: Newborn Individualized Developmental Assessment Program
OR: Operation room
PDA: Persistent ductus arteriosus
PMA: Postmenstrual age
PVL: Periventricular leukomalacia
SBT: Simulation-based training
SC: Standard care
SSC: Skin-to-skin care
STAI: State-Trait Anxiety Inventory
